## Abstract

**Introduction:**

Nocturnal blood pressure (BP) appears to be a better predictor of cardiovascular outcome than daytime BP. The BP lowering effects of most antihypertensive therapies are often greater in the first 12 h compared to the next 12 h. The Treatment In Morning versus Evening (TIME) study aims to establish whether evening dosing is more cardioprotective than morning dosing.

**Methods and analysis:**

The TIME study uses the prospective, randomised, open-label, blinded end-point (PROBE) design. TIME recruits participants by advertising in the community, from primary and secondary care, and from databases of consented patients in the UK. Participants must be aged over 18 years, prescribed at least one antihypertensive drug taken once a day, and have a valid email address. After the participants have self-enrolled and consented on the secure TIME website (http://www.timestudy.co.uk) they are randomised to take their antihypertensive medication in the morning or the evening. Participant follow-ups are conducted after 1 month and then every 3 months by automated email. The trial is expected to run for 5 years, randomising 10 269 participants, with average participant follow-up being 4 years. The primary end point is hospitalisation for the composite end point of non-fatal myocardial infarction (MI), non-fatal stroke (cerebrovascular accident; CVA) or any vascular death determined by record-linkage. Secondary end points are: each component of the primary end point, hospitalisation for non-fatal stroke, hospitalisation for non-fatal MI, cardiovascular death, all-cause mortality, hospitalisation or death from congestive heart failure. The primary outcome will be a comparison of time to first event comparing morning versus evening dosing using an intention-to-treat analysis. The sample size is calculated for a two-sided test to detect 20% superiority at 80% power.

**Ethics and dissemination:**

TIME has ethical approval in the UK, and results will be published in a peer-reviewed journal.

**Trial registration number:**

UKCRN17071; Pre-results.

Strengths and limitations of this studyUse of technology including an electronic case report form and record linkage to identify potential end points allows efficient data management.The open-label design provides good external validity. The end-point committee is blinded to treatment randomisation.Limitations include the generalisability of results based on participants who have an email address and are technologically literate.

## Introduction

Nocturnal blood pressure (BP) has consistently been found to be a better predictor of cardiovascular outcome than daytime BP. As the day:night BP ratio increases, cardiovascular risk appears to decrease.^1–4^ There is also evidence to suggest that antihypertensive drugs taken in the evening rather than in the morning reduce nocturnal blood pressure to a greater extent,^5–7^ and might have more benefit in hypertension alone^8^
^9^ hypertension with renal disease^10^
^11^ and hypertension with diabetes.^12^ A recent study that examined the effect on nocturnal blood pressure of drugs taken in the evening in participants with resistant hypertension found that bedtime dosing resulted in significantly lower 24 h means of systolic and diastolic BP (by 4.1/1.5 mm Hg) and that this difference between groups was driven by asleep BP (9.7/4.4 mm Hg lower).^13^ The most recent and most compelling evidence in favour of nocturnal dosing comes from the Monitorización Ambulatoria para Predicción de Eventos Cardiovasculares (MAPEC) study which randomly assigned 2156 hypertensive patients to take all of their antihypertensive drugs on awakening or to take one or more of them at bedtime.^14^
^15^ All patients in this study underwent ambulatory blood pressure monitoring (ABPM) at baseline and yearly, and all wore wrist activity metres to control for the effects of activity on BP and to determine when participants were asleep.^16^ Participants in the study who took one or more antihypertensive drugs at bed-time had 68 cardiovascular events whereas those who took all medication on awakening had 187 events; a relative risk reduction of 64% (p<0.001). Forty-eight-hour ABPM showed lower systolic BP (122.1 mm Hg morning dosing vs 120.8 mm Hg evening dosing p=0.029) with evening dosing and this difference was due to lower asleep systolic blood pressure (116.1 mm Hg morning dosing vs 110.9 mm Hg evening dosing, p<0.001). The MAPEC study was limited in that it was not prospectively powered, the process of randomisation was not reported, and the end points included some unusual cardiovascular events, and were not independently adjudicated.

Further studies are needed to establish the optimal time of dosing for hypertensive patients.^17^
^18^ Therefore, the present study aims to substantiate the findings of the MAPEC study and test the hypothesis that nocturnal dosing of antihypertensive medication reduces cardiovascular events compared with conventional morning dosing. Secondary questions will examine whether there are any downsides to nocturnal dosing and if nocturnal dosing is acceptable to patients, for example, whether nocturnal dosing of diuretics causes unacceptable nocturia will be evaluated. Data will also be collected on nocturnal hypotension and its consequences (eg, falls and fractures).

## Methods

### Trial design

The Treatment In Morning versus Evening (TIME) study is a prospective, randomised, open-label, blinded end-point (PROBE) design^19^ controlled clinical trial. TIME (http://www.timestudy.co.uk) builds on a successful novel methodology to track patient outcome using information technology (IT). The project will be conducted on a secure web portal with patients signing up on-line and being followed up by email and record-linkage to national databases to identify hospitalisations and deaths.^20^
^21^ End points will be detected by record-linkage to hospitalisation, death certification records and regular email contacts with patients and nominated surrogates. Primary or secondary care records and physicians will be contacted for further data, if required (all patients must consent to their medical records and physicians being accessed or contacted). All end-point adjudication will be blinded to dosing time and original medical records will be retrieved for hospitalisation events to validate end points. The schematics and flow of the study can be seen in figures 1 and 2. The TIME study underwent a pilot phase between 2011 and 2014 to determine feasibility of a full study. At that time the study was not adopted by the UKCRN and so trial registration was not possible. There were doubts as to the viability of the study being conducted online and whether there would be sufficient recruitment uptake. Once the study was deemed sustainable, funding was in place, and the clinical trials networks adopted the study, it was prospectively registered in ISCRTN and the pilot transferred to the full study.

**Figure 1 BMJOPEN2015010313F1:**
[figure not shown]
Schematic diagram of study.

**Figure 2 BMJOPEN2015010313F2:**
[figure not shown]
TIME study flow diagram.

### Recruitment strategy

In an effort to recruit the necessary number of participants, the full study will seek to recruit by advertising to hypertensive patients in the UK from primary care, secondary care and from databases of patients who have previously consented to being contacted about potential research projects. Collaborating general practitioners (GPs) will bring this trial to the attention of all treated hypertensive patients in their practices by sending letters advertising the study. Secondary care clinics will also send letters advertising the study to previous clinic attendees and display advertising posters in appropriate patient waiting areas. Databases of consented patients will be utilised where appropriate, such as UK Biobank,^22^ Tayside Bioresource and GoShare,^23^ contacting patients and advertise the study to them. The Database owners will send approved letters on behalf of TIME. The inclusion and exclusion criteria for TIME are listed in boxes 1 and 2. Potential study participants are invited to complete an initial online study registration. This process requires them to confirm their eligibility against the study inclusion and exclusion criteria before allowing them to proceed and complete enrolment.
Box 1TIME inclusion criteriaInclusion criteriaBoth diagnosed and treated for hypertension (all forms) with at least one antihypertensive drug.Age ≥18 years.Have a valid email address.
Box 2TIME exclusion criteriaExclusion criteriaParticipants who take two times a day antihypertensive therapy.Participants who work shift patterns that include a night shift.Participants who are unwilling to consent to:
Follow-upProviding a surrogate to be contacted and/orTheir family practice releasing follow-up clinical dataTheir physical case records abstracted if requiredTheir electronic case records searched and abstracted if requiredTheir consent form to be copied to authorities from whom the study team is requesting medical data.Those participating in another clinical trial or who have done in the past 3 months.

### Intervention

Participants within the study are randomly allocated to one of two dosing periods. Participants allocated to morning dosing are advised to take all of their usual blood pressure lowering medications between 6:00 and 10:00 throughout the study. Those allocated to evening dosing are instructed to take all their blood pressure lowering medications between 20:00 and midnight. There is no other intervention in the study and participants continue to attend their usual GP or outpatient clinic for routine hypertension follow-up.

### Follow-up

Patients will be followed up after 1 month of being assigned a randomised time of dosing, and then every 3 months. Contact will be made by automated email with a reminder email sent 14 days later. If the follow-up has still not been completed then 14 days after the first email reminder has been sent an email will be sent to the participant's surrogate asking them to respond as to the well-being of the participant. As a last resort, telephone calls to patients or primary care physicians can be used to contact participants and to ask them to complete follow-ups. Participants can enter follow-up data at any time during the trial by logging into the secure website and are not restricted to waiting for automated emails. A final record linkage will be performed 3 months after the end of the trial in order to capture late recorded events and a final 3 months will be spent finalising adjudications, locking the database and carrying out the analysis.

### Consenting participants

Patients will be required to fill in an electronic consent form (figure 3). The consent form will consist of check boxes to attest to consent for each aspect of the trial. A final check box will be marked ‘I have read, answered and understood all of the above questions and understand this is an electronic signature’. The consent form will record the participant's internet protocol (IP) address along with their email address and a time stamp of when the form was electronically submitted. The consent form will be sent to participants electronically in portable document format (PDF) format for their own records. The decision of a participant to participate in clinical research is voluntary and will be based on a clear understanding of what is involved. A patient information sheet will be available on the TIME website with detailed information about the trial. The consent process will be conducted by participants and entirely via the study website, without the active participation of study personnel. Participants will be given opportunities to clarify any points they do not understand, and to ask for more information by using a ‘Contact Us’ link, or the free phone telephone number, on the study website.

**Figure 3 BMJOPEN2015010313F3:**
[figure not shown]
Consent form.

### Withdrawal

Participants will be free to withdraw from the TIME study at any point. A participant can withdraw from:
Taking medication according to the time of randomisation.Receiving further follow-up emails.Follow-up of their outcome by record linkage, contacting their surrogate or by contacting their family doctor.

Part of the objective of this study is to determine if subjects can continue to take medication at their randomly allocated time, and indeed, we expect that a proportion of participants will withdraw from taking medication at their allocated time. We shall evaluate the withdrawal rate and record reported reasons for their withdrawal.

## Randomisation

### Computer randomisation

Randomisation is carried out centrally using randomly generated bits (0 and 1 s) which are then allocated to participants (0=morning, 1=evening) sequentially. Randomised status is confirmed by automated email sent to the participant.

### Treatment allocation

Participants are randomised to take their antihypertensive medications in the morning (range 6:00–10:00) or in the evening (range 20:00–midnight). Treatment allocation is not made available to treating physicians unless there is a specific individual clinical need.

### Study population

Hypertensive patients aged 18 or over, in the UK, prescribed one or more once daily antihypertensive drug therapies, and, who have a valid email address (see box 1).

## Trial end points

### Primary end point

The primary end point is first occurrence after randomisation of vascular death or hospitalisation for the composite end point of non-fatal MI or non-fatal stroke, in keeping with major cardiovascular disease (CV) end-point trials.^24^

### Secondary end points

Secondary end points (in rank order) will include:
Each component of the primary end point:
Hospitalisation for non-fatal strokeHospitalisation for non-fatal MICardiovascular deathAll-cause mortalityHospitalisation or death from congestive heart failure.

### End-point adjudication

End points will be adjudicated by an independent end-point committee who will be blind to dosage time allocation. Hospitalisation data will be retrieved in collaboration with the medical records departments. Copies of the patient consent forms will be supplied to facilitate this process. The records will be processed, abstracted and suitably redacted to produce anonymised end-point packages for the end-point committee. This committee will have due regard of the published consensus diagnostic criteria for myocardial infarction,^1^
^25^ stroke,^26^ vascular death, and heart failure.^27^

### Adverse events

Recording of serious adverse events (AEs) will focus on deaths and hospital admissions as these will be obtained systematically by record linkage. The present study will collect only non-serious AEs associated with changing the time of dosing. Follow-up (figure 4) and withdrawal (figure 5) questionnaires include a mix of open and closed questions regarding medical events and potential AEs. In the case of an AE, patients will judge whether they are happy to continue taking treatment at the time randomised or whether they wish to change or revert to the alternative time of dosing, or, whether they wish to discontinue the study.

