**Figure 5 BMJOPEN2015010313F5:**
[figure not shown]
Withdrawal form.

An additional reason for carrying out the study is to determine whether participants can tolerate taking medication in the evening. This is prospectively measured. Participants self-report AEs associated with dosing time and whether nocturnal diuretic dosing has been acceptable to them and whether falls and fractures are increased as a potential surrogate for nocturnal hypotensive events.

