### Statistics

The primary outcome will be a comparison of time to first event comparing morning versus evening dosing allocation. This outcome will be analysed using a Cox proportional hazards model including treatment group as a covariate. The p value for the treatment effect will be based on the Wald statistic. Point estimates and 95% CIs will be calculated for the treatment effect HR. Time to event curves will be based on cumulative incidence functions. Time to event secondary outcomes will be analysed using similar methods. The proportionality of hazards assumptions will be assessed using Cox models including treatment group by log (time) interactions.

Serious AEs and AEs will be tabulated by treatment group by system organ class and preferred term. All main analyses will be on an intention-to-treat basis.

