## Discussion

The trial design of TIME allows a large study to be undertaken efficiently and cost-effectively by maximising the benefits of modern technology, including use of an electronic case report form and following up patients using record linkage. All data are entered directly by participants, thereby helping to reduce researcher time and costs. Participant's GPs are made aware of their participation in the study but there is no significant workload implication and GPs are not required to submit data. The study allows participants to self-enrol, consent and provide data in a secure online environment. The TIME study has been awarded a grant from the BHF to write to 300 000 patients across the UK to achieve its target of randomising over 10 000 participants.

If the TIME study shows definite benefits of dosing antihypertensive medication in the evening rather than the morning, this would represent the most cost-effective advance in the treatment of hypertension and the prevention of CV disease in recent years. TIME will also establish whether participants can tolerate nocturnal dosing and whether there are any AEs of nocturnal versus morning dosing.

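### Non-serious adverse events are collected under two different rules, and the narrower one, read literally, could record fewer events in the morning arm

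*Protocol article*

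**What the plan says.** All references are to the protocol article.

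- Adverse events, first paragraph, gives the collection rule: "The present study will collect only non-serious AEs associated with changing the time of dosing". The next sentence says that the follow-up and withdrawal "questionnaires include a mix of open and closed questions regarding medical events and potential AEs". Serious events are treated separately, through deaths and admissions found by record linkage.
- Adverse events, paragraph after Figure 5, describes the collection differently: "Participants self-report AEs associated with dosing time and whether nocturnal diuretic dosing has been acceptable to them". The same sentence adds, as a further item, "whether falls and fractures are increased as a potential surrogate for nocturnal hypotensive events".
- Statistics gives the analysis: "Serious AEs and AEs will be tabulated by treatment group by system organ class and preferred term".
- Discussion gives the intended conclusion: "TIME will also establish whether participants can tolerate nocturnal dosing and whether there are any AEs of nocturnal versus morning dosing".
- Introduction frames the trial hypothesis as evening dosing "compared with conventional morning dosing". The inclusion criteria (Box 1) require existing antihypertensive treatment but set no condition on when it is currently taken. The article gives no figure for the share of participants already dosing in the morning.

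**The concern.** The two descriptions of what is collected are not the same. One ties a reportable event to a change of dosing time; the other ties it to dosing time. The difference matters because whether a change occurs depends on the allocated arm. A morning doser allocated to evening changes. A morning doser allocated to morning does not, and under the narrower rule cannot have a reportable non-serious event.

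If morning dosing was the usual habit at baseline, the narrow rule would draw non-serious events mostly from the evening arm. A table by randomised group would then show an excess with evening dosing even if both times were equally well tolerated. Symptoms among people who simply stay on morning dosing would go unrecorded. Whether evening dosing has downsides is a stated secondary question of the trial, and events that were never collected cannot be recovered at analysis.

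**Working it through.** **Figures in the plan.** The article states no adverse event rate, no capture rate and no baseline dosing share, so there is no design figure to reproduce on this point. The only input taken from it is the target of 10 269 participants (Sample size section; 9780 × 1.05 = 10 269). Allocation by random bits gives about 10 269 / 2 ≈ 5134 per arm. Everything else below is an assumption shown over a range.

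**Step 1: who changes.** Let m be the share dosing in the morning before randomisation, with the rest dosing in the evening. Randomisation balances m between arms, so the share who must change is m in the evening arm and 1 − m in the morning arm.

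**Step 2: recorded risk.** Let p be the true event risk, equal in both arms and the same in changers and non-changers. Let c be capture in non-changers relative to changers (0 = nothing recorded, 1 = recorded alike).

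- Evening arm: p × [m + c(1 − m)]
- Morning arm: p × [(1 − m) + cm]

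**Step 3: literal narrow rule (c = 0).** The ratio is m / (1 − m), whatever p is. With p = 10%:

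| m | Evening recorded | Morning recorded | Ratio (true ratio 1) |
|---|---|---|---|
| 50% | 5% | 5% | 1.0 |
| 60% | 6% | 4% | 1.5 |
| 70% | 7% | 3% | 2.3 |
| 80% | 8% | 2% | 4.0 |
| 90% | 9% | 1% | 9.0 |

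Below 50% the direction reverses: m = 40% gives 0.4 / 0.6 = 0.67.

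**Step 4: same questions and recording for all (c = 1).** Both expressions reduce to p, and the ratio is 1.0 at every m.

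**Step 5: partial capture.** With m = 80% and c = 0.5, the evening factor is 0.8 + 0.1 = 0.9, the morning factor is 0.2 + 0.4 = 0.6, and the ratio is 1.5.

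**Step 6: how visible a modest imbalance would be.** Suppose overall capture in the morning arm is 75% of that in the evening arm, and the true risk is 10%. Recorded risks are 10% and 7.5%, an apparent risk ratio of 1.33. The standard error of the difference is √[(0.10 × 0.90 + 0.075 × 0.925) / 5134] = 0.0056, and 0.025 / 0.0056 ≈ 4.5. The chance of a spurious two-sided p < 0.05 is therefore about 99%. At a true risk of 5% (5% against 3.75%) it is about 87%. The article announces a tabulation and names no test for adverse events, so these figures only show how large the false signal would look.

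**The case against.** The case against rests on the surrounding text, and much of it stands.

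- **A reader might infer that the morning arm is under-counted by design and that bias against evening dosing is certain.** The article does not establish this. The sentence after the narrow rule describes broad questionnaires, one follow-up schedule serves all participants, no question is said to be confined to one arm, and the paragraph after Figure 5 uses the wider criterion. The forms themselves (Figures 4 and 5) are not visible in the text at hand. If both arms answer the same form and answers are recorded alike, the bias does not arise.
- **A reader might take the ratio of 9 as an estimate.** It needs both a 90% morning share and no capture at all in non-changers. The article supports neither figure. The description of morning dosing as conventional suggests a majority but does not measure it, and evening dosers allocated to morning are changers too.
- **A reader might extend the point to falls and fractures.** These are listed as a separate self-report item, and the Introduction separately commits to collecting them. Neither statement makes them conditional on a change.
- **A reader might say the withdrawal comparison has the same flaw.** The Withdrawal section says "We shall evaluate the withdrawal rate and record reported reasons for their withdrawal". Withdrawal is open to and counted in every participant in either arm, so ascertainment is not unequal. That section asks whether people can keep to their allocated time, and the burden of switching is part of that question.

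What survives is that the narrow rule is worded as exclusive, and nothing in the article says that the wider description or the questionnaires override it. If the forms already treat everyone alike, the sentence misdescribes the trial and still needs replacing. The wider criterion also leaves unblinded participants to decide what is linked to dosing time, which someone newly moved to the evening has more reason to do.

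**Conclusion.** The concern holds in a limited form. The article defines the collected non-serious adverse events in two ways. Followed literally, the narrower definition makes capture depend on allocated arm unless baseline dosing time is split evenly. The likely direction is against evening dosing, on the unquantified assumption that most participants dosed in the morning beforehand. The size is unknown: the recorded ratio runs from 1.0 to 9.0 over baseline shares of 50% to 90% with no capture in non-changers, and is 1.0 throughout under equal questioning and recording.

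Only the non-serious event table and the tolerability conclusion drawn from it are at risk. Serious events from record linkage are unaffected, as are the primary and ranked secondary end points, which rest on linked and blindly adjudicated hospitalisations and deaths. The inconsistency is worth correcting and does not threaten the main result.

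**What to change.** Replace the narrow sentence in Adverse events and align it with the paragraph after Figure 5, so that a single rule applies. The same non-serious adverse event questions are put to all participants in both arms at every follow-up. Answers are recorded the same way whether or not dosing time changed, and the participant is not required to attribute the event to a change. If the existing forms already work this way, only the wording needs correcting.

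Record usual dosing time before randomisation, so that the adverse event comparison by arm can also be shown by previous dosing time. This separates an effect of evening dosing from an effect of having switched.

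The cost is a rewording, one enrolment question and a larger number of non-serious event records to code. The change has to apply prospectively.
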